**Table 1: Schedule of enrolment, interventions and assessment**

|  | | | **STUDY PERIOD** | | | |
| --- | --- | --- | --- | --- | --- | --- |
|  | | | **Baseline** | **Intervention** | **Follow-up**  **1** | **Follow-up**  **2** |
| **Timepoint** | | | **1** |  | **2** | **3** |
| **Month** | | | 0 |  | 1 | 2 |
| **Sample description** | | |  |  |  |  |
|  | Family characteristics and demographics | | X |  |  |  |
| **Outcomes** | | |  |  |  |  |
|  | Child | SDQ conduct problems | X |  | X | X |
|  |  | SDQ emotional problems | X |  | X | X |
|  | Parent | Parental child-related stress and worries | X |  | X | X |
|  |  | Family conflict | X |  | X | X |
|  |  | DASS-21 psychological distress | X |  | X | X |
| **Other measures** | | |  |  |  |  |
|  | SDQ ADHD symptoms | | X |  | X | X |
|  | SDQ peer problems | | X |  | X | X |
|  | SDQ prosocial behaviour | | X |  | X | X |
|  | CA-SUS service utilisation | |  |  | X | X |
|  | Lockdown circumstances | | X |  | X | X |
|  | Self-reported adverse events | |  |  | X | X |
| **Interventions randomised 1:1** | | |  |  |  |  |
|  | *Parent Positive* | |  | Access to app | | |
|  | Follow-up As Usual^a^ | |  | No access to app | | |
| **Intervention usage and acceptability** | | |  |  |  |  |
|  | Total time spent accessing the *Parenting Boosters* | |  |  | X | X |
|  | Other app usage metrics | |  |  | X | X |
|  | Parent Positive Attitudes | |  |  | X | X |
| *Note.* CA-SUS=Child and Adolescent Service Use Schedule; DASS-21=Depression, Anxiety & Stress Scale-21; SDQ=Strengths and Difficulties Questionnaire.  ^a^=Parents allocated to Follow-up As Usual will get access to Parent Positive after the Follow-up 2 (T3) assessment. | | | | | | |

- - 1. **Emotional problems (T1 co-variate, T2 and T3 secondary outcome; T1 moderator):** measured by the respective SDQ subscale (Goodman, 1997). This five-item subscale measures fearfulness, anxiety and low mood rated on a 3-point Likert scale (not true, somewhat true, and certainly true) with positively phrased items. Individual items’ scores are summed to derive an overall symptoms subscale score.
  1. **Parent/family outcome**
     1. **Parental child-related stress and worries levels (T1 co-variate; T2 and T3 secondary outcomes):** This is based on five items routinely measured in Co-SPACE regarding children’s behaviour, wellbeing, screen time use, education and future using a 4-point Likert scale (not at all, a little, quite a lot, a great deal). Individual questions’ scores are summed to generate a single score. The scale has an adequate level of internal consistency (Cronbach alpha > .70) and re-test reliability (*r* = .71) amongst Co-SPACE parents.
     2. **Family conflict (T1 co-variate; T2 and T3 secondary outcomes):** This is based on three items routinely collected in Co-SPACE relating to arguments between parents, parents and children and siblings which are measured on a 4-point Likert scale (not at all, a bit, a lot, completely). The three questions are summed to generate a total score. The scale has acceptable internal consistency (Cronbach alpha > .54) and test-retest reliability (*r* = .73) amongst Co-SPACE parents.
     3. **Parental psychological distress (T1 co-variate; T2 and T3 secondary outcome; T1 moderator):** The Depression, Anxiety and Stress Scales-21 (DASS-21) is a widely validated 21-item self-report questionnaire measuring adult depression, anxiety and stress (Lovibond & Lovibond, 1995). Each of these three subscales consists of seven items rated on a 4-point Likert scale (did not apply to me at all; applied to me to some degree, or some of the time; applied to me to a considerable degree, or a good part of the time, applied to me very much, or most of the time), which are summed to obtain a single subscale score. The subscales scores will be summed and multiplied by two to form a single psychological distress measure comparable to the DASS-42 measure.
  2. **Other measures**
     1. **ADHD symptoms (T1 moderator; T1, T2 and T3 for QALYs calculation)**: measured with the inattention/overactivity subscale of the SDQ (Goodman, 1997). This five-item subscale measures restlessness, overactivity and inattention rated on 3-point Likert scales (not true, somewhat true, and certainly true), with a mix of positive and negatively phrased items. Individual items’ scores are summed to derive an overall symptoms subscale score.
     2. **Peer problems (T1, T2 and T3 for QALYs calculation)**: measured with the peer problems subscale of the SDQ (Goodman, 1997). This five-item subscale measures difficulties in peer relationships and bullying rated on 3-point Likert scales (not true, somewhat true, and certainly true), with a mix of positive and negatively phrased items. Individual items’ scores are summed to derive an overall peer problems subscale score.
     3. **Prosocial behaviour (T1, T2 and T3 for QALYs calculation)**: measured with the prosocial behaviour subscale of the SDQ (Goodman, 1997). This five-item subscale measures difficulties in peer relationships and bullying rated on 3-point Likert scales (not true, somewhat true, and certainly true), with positively phrased items. Individual items’ scores are summed to derive an overall prosocial subscale score with higher scores indicating more prosocial behaviour.
     4. **Attitudes to Parent Positive (T2 and T3, intervention arm only):** Parent mean ratings of *Parent Positive* using a questionnaire, consisting of three items measuring parents’ ratings of the usefulness of each individual zone rated on a 7-point scale (1 = not useful at all to 7 = very useful), which will be summed up to derive an overall app usefulness score. The questionnaire will also capture parents’ descriptive and qualitative views of *Parent Positive* – both positive and negative.
     5. **Estimate of resource use for the health economic analysis (T2 and T3):** Information about the child’s use over the two-month follow-up period of key health and social services (high cost, high volume) known from published studies to be of relevance to the current population will be collected using a modified version of the Child and Adolescent Service Use Schedule (CA-SUS; Barrett et al., 2012). The CA-SUS will be completed by the parent at T2 and T3, covering the previous month. This measure has been developed and successfully applied in a range of populations of young people with mental health conditions, including self-complete versions, and will be based primarily on an online, self-completed parent-reported version of the CA-SUS designed for use in a current, related study (the NIHR funded OPTIMA trial - On-Line Parent Training for the Initial Management of ADHD referrals; RP-PG-0618-20003).
     6. **App usage data (During intervention period, intervention arm only):** Usage data will be broken down by *Parent Positive* elements (challenges) and domains (Boosters, Exchange, Resources). This will allow descriptive analysis of usage patterns. The analysis of the impact of usage levels on the effects of *Parent Positive* (see analysis section below) variables will be based on a derived measure of total time accessing the “Boosters” zone during the one month intervening period. Other app usage metrics will be collected (e.g., engagement in Exchange zone).
     7. **Family characteristics and demographic measures (T1 co-variates; sample description):** Parents will provide information about their child’s age and gender, their own and their child’s ethnicity, number of children in the family, number of rooms in the family home and access to outside space. This information will be used to describe the sample and an overcrowding index will be calculated by dividing the number of individuals in the household by the number of rooms. We will estimate family SES based on total household income, coded as < £16,000 | £16,000 - £29,999 | £30,000 - £59,999 | £60,000 - £89,999 | £90,000 - £119,999 | > £120,000 | Prefer not to say, likely collapsing small categories.
     8. **COVID-19 pandemic lockdown circumstances (T1 moderator; T2 descriptives; T3 descriptives):** Parents will provide information on the pandemic-related restrictions they are currently facing. This will include details of the current lockdown policy in their local area (partial or full lockdown), whether parents are working from home, and whether children are being home-schooled.

1. **Time schedule of enrolment and assessment**

Recruitment for the trial will be between April to July 2021. Final T3 assessments will be concluded in September 2021. The enrolment and group allocation procedure is shown in Figure 1. All parents aged 18+ of children aged 4-10 years completing the Co-SPACE survey between April and July 2021 will receive an invitation to take part in SPARKLE – this will appear at the beginning of the Qualtrics survey. Parents who express interest in taking part will be provided with an information sheet about the SPARKLE trial and those who wish to take part will be provided with an online consent form to be completed within Qualtrics. Prior to consenting, parents will be asked to confirm that they have access to a compatible smartphone. Consenting parents will be randomised within Qualtrics using a Randomizer tool and followed-up using a separate survey branch. Qualtrics will automatically inform the parent about their group allocation. A researcher responsible for providing participants with instructions regarding the app access will obtain information about the outcome of randomisation from the Qualtrics database.

[figure not shown]

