3. The *Parent Resources* zone will provide links to carefully selected high-quality, evidence-based online parenting resources reviewed and approved by a committee of parenting experts.

The app will be free and parents will be able to access the information when needed and in the order they choose. Parents in the intervention group will receive access during the immediate post-randomisation period until 30^th^ November 2021. To access the app, parents will receive an automated email with a link to download it from either Google Play (for Android users) or the App Store (for Apple users) together with brief instructions on how to download the app on the smartphone and register as a user.

- 1. **Follow-up as Usual (FAU):** FAU was selected as a comparator because the public health nature meant that an active comparator was not appropriate due to the pragmatic, rapid deployment of the trial. Individuals randomised to FAU will receive no intervention for the first 10 weeks while the data for baseline (T1), T2 and T3 are collected. They will then be given full access to the app until 30^th^ November 2021.
  2. **Criteria for discontinuing intervention.** We do not expect using *Parent Positive* to lead to harm that would suggest the intervention needs to be discontinued. However, parents will be able to withdraw from the trial at any point for any reason.
  3. **Strategies to increase engagement with the app and levels of app usage.** The traditional notion of adherence to an intervention protocol does not apply to public health intervention trials where samples are not restricted to those with a specific clinical need. This is the case in SPARKLE where we expect that a significant proportion of parents who are enrolled in the trial may not feel they need to use the app (i.e., those not having difficulties parenting their children’s behaviour). Nevertheless, we will initially encourage parents to use the app and promote high levels of engagement using push notifications on their mobile phone reminding them to engage with *Parent Positive*. Including the Parenting Exchange in the app is also expected to improve engagement. First, participants will be able to communicate with each other by posting and reading messages. Second, they will receive social feedback from their peers on their posts made within the Exchange. Third, they will be able to ask questions to experts via the Exchange.

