It is not possible to blind parents enrolled in the study and Qualtrics will automatically inform parents of their group allocation. Data will be collected remotely by Qualtrics. Blinded members of the research team and the senior statistician will not be given access to the Qualtrics system or the data in order to remain blinded until after the analysis is complete. We do not anticipate any serious harms associated with taking part in the intervention, therefore there will be no need to unblind any blinded staff during the study. The junior statistician will be unblinded throughout.

1. **Data collection**

SPARKLE data will be collected at monthly intervals at three time points following the Co-SPACE schedule as indicated above (Baseline [T1], T2, and T3) using the Qualtrics platform. Finally, in SPARKLE, *Parent Positive* usage data will be collected automatically within the app across the intervention period as described above.

1. **Data management**

Handling of the data collected in Co-SPACE is described in detail in the Co-SPACE Data Management Plan. The SPARKLE Data Management Plan outlines how SPARKLE-specific data collected outside of the Co-SPACE routine follow-ups will be managed and stored during and after the project is completed. The junior statistician will request periodic data extracts from the Co-SPACE (baseline) and SPARKLE (follow-up) teams; these will be shared via a restricted OneDrive for Business link, then moved to King’s College SharePoint location, which is a web-based, Microsoft Office integrated collaborative platform. The data provided from Co-SPACE will be linked to the *Parent Positive* usage data using the SPARKLE ID. The data stored on SharePoint are encrypted and access to the data will be restricted only to those who need to have it.

1. **Statistical analysis**

**Aim i) Does *Parent Positive* reduce the average levels of parent-reported child conduct problems in a self-selected community sample, measured over a one (primary outcome) and two month (secondary outcome) period, when compared to Follow-up As Usual (FAU)?**

**Aim ii) Does *Parent Positive* reduce the average levels of parent psychological distress, parental child-related stress and worries, family conflict and child emotional problems (additional secondary outcomes) in a self-selected community sample, measured over a one and two month period, when compared to FAU**?

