Serious adverse event (SAE): Any AE, which results in death, is life-threatening, requires hospitalisation or prolonged hospitalisation, causes persistent or significant disability or incapacity, or consists of a congenital abnormality or birth defect. Important medical events that may not be immediately life-threatening or result in death or hospitalisation but may jeopardise the patient or may require intervention to prevent one of the other outcomes listed in the definition above should also be considered serious.

Psychological events: Self-reported emergence or a substantial increase in detrimental behaviour or circumstance including: child behaviour, child participation in school or extra-curricular activities, parent psychological distress, family conflict, and child protection concerns. Parents will also be asked whether they have experienced any other negative/positive events that they feel are important to their participation in the trial.

Adverse events will be asked about at T2 and T3 and reported retrospectively covering the previous month. All reported events will be reviewed by the research team to identify any SAEs. All SAEs will be recorded and closely monitored until resolution, stabilisation, or until it has been shown that the study intervention is not the cause.

1. **Auditing**

Auditing is not applicable to this protocol.

1. **Ethics**

All relevant study documents have been reviewed and approved by the King’s College London – Psychiatry, Nursing and Midwifery Research Ethics Subcommittee, reference number HR-20/21-21451 and the University of Oxford Central University Research Ethics Committee, reference numbers R73153/RE001. Any future protocol amendments will be documented and submitted for ethical approval prior to implementation. No recruitment activity took place before ethical approval for the study had been obtained. Co-SPACE ethical approval was granted by the University of Oxford Central University Research Ethics Committee, reference numbers R69060/RE001.

1. **Protocol amendments**

In case of new information becoming available, which may result in significant changes to the risks and benefits of taking part, the PIS and informed consent form will be reviewed and updated accordingly. All parents actively enrolled in the study will be informed of the updated information and will be given a revised copy of the PIS and informed consent form to confirm their wish to continue taking part.

1. **Consent**

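### The fixed one-month recall for service use and adverse events means that a parent who misses T2 but answers T3 is never asked about month 1

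*Protocol*

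**What the plan says.** Three parts of the Protocol bear on this.

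- **Measures and Outcomes, Other measures (resource use).** The data wanted are "Information about the child’s use over the two-month follow-up period of key health and social services". The collection rule is "The CA-SUS will be completed by the parent at T2 and T3, covering the previous month". No other source of service-use data is named.
- **Harms.** "Adverse events will be asked about at T2 and T3 and reported retrospectively covering the previous month". Serious events are picked out of these reports: "All reported events will be reviewed by the research team to identify any SAEs".
- **Data collection and Table 1.** "SPARKLE data will be collected at monthly intervals at three time points following the Co-SPACE schedule". Table 1 places T2 at month 1 and T3 at month 2, and schedules the CA-SUS and self-reported adverse events at those two points only.

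Statistical analysis, Aim iv, sets the cost-utility analysis at two months. Interventions (permitted concomitant care) also relies on the service-use and harms data to monitor other care. The Protocol gives no response window for T2 or T3, and no different recall at T3 for a parent who did not complete T2.

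**The concern.** The period that must be covered is defined from randomisation, but each questionnaire looks back a fixed month. The two agree only if every parent completes both surveys close to schedule. Collection is remote and self-completed, and the Sample section plans for 30% drop-out, so some missed surveys are to be expected.

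Two things are at stake. For the economic analysis, a parent who is answering at T3 and could report on month 1 is not asked to, so an obtainable value has to be imputed. For harms, the loss is final: imputation can stand in for a cost, but it cannot disclose an event nobody asked about. T2 and T3 are the only scheduled points at which adverse events are asked about, and there is no separate data monitoring committee, so these reports carry most of the safety information in the trial.

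**Working it through.** The plan states no figure for coverage of follow-up, so there is none to reproduce. The sample size of 616 rests on the SDQ conduct score and does not enter this check.

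**Inputs.** From the Protocol: T2 at month 1, T3 at month 2, and a recall of one month at each. Assumed: one month is W = 30.4 days, so two months is about 61 days; the recall is counted back from the day the survey is answered, which the Protocol does not say.

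**Formulas.** Let t2 and t3 be the days on which the surveys are answered.

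- Both answered: days uncovered = max(0, t2 − W) + max(0, t3 − W − t2); days counted twice = max(0, t2 − (t3 − W)).
- T2 missed: days uncovered = t3 − W.

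**Both on time (t2 = 30, t3 = 61).** Uncovered = 0 + (61 − 30.4 − 30) = 0.6, at most about 1 day. Counted twice = 0. The rule works as intended.

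**T2 missed, T3 on time (t3 = 61).** Uncovered = 61 − 30.4 = 30.6, about 31 of 61 days, or half of follow-up. The result hardly depends on the counting-back assumption: with T3 on time, a month counted back from the scheduled date is the same month.

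**Late answers, mechanism only.** Take t2 = 40 and t3 = 61, where day 40 is invented for illustration. Uncovered = 40 − 30.4 = 9.6, about 10 days at the start. Counted twice = 40 − (61 − 30.4) = 9.4, about 9 days. A late T2 can therefore produce a gap and an overlap together. This is not an estimate: the Protocol gives neither response times nor a response window.

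**With the recall started at joining or at the last completed survey.** T2 covers day 0 to t2, and T3 covers t2 to t3, or day 0 to t3 if T2 was missed. Uncovered and doubly counted days up to the last completed survey are 0 in each case above.

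**Number of parents.** The 30% drop-out in the Sample section does not separate parents who leave for good from those who skip T2 and return. No headcount can be derived from it.

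**The case against.** The best defence is that the design is coherent as scheduled. Two one-month recalls at months 1 and 2 cover the two months, and a missed survey is ordinary missing data, whose handling belongs in an analysis plan. A short, uniform recall also limits memory error and keeps measurement the same for every parent. Exact item wording belongs to the survey instrument, which is not shown. No serious harms are anticipated, and no safety stopping rule depends on these reports.

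Part of this stands. On-time responders lose nothing, missing costs can be imputed, and a longer recall is a real trade-off. But the recall length is not a detail left open: the Protocol fixes it in two places. An analysis plan cannot supply an adverse event that was not asked about. The longer recall falls only on parents who would otherwise give no month-1 information.

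Stronger readings are tempting, and the document does not support them:

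- A reader might set two one-month recalls against the statement "Individuals randomised to FAU will receive no intervention for the first 10 weeks while the data for baseline (T1), T2 and T3 are collected" and infer that a fixed share of follow-up is lost for late responders. That sentence governs app access in the control arm. It is not a response window and says nothing about the Parent Positive arm. The economic horizon is two months, not ten weeks.
- A reader might infer that costs will be biased low because a blank month is read as zero use. No section says that this will be done.
- A reader might infer unequal loss of harms between the arms. This is possible if T2 response differs by arm, but nothing in the Protocol shows that it will.

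**Conclusion.** The point holds for the parent who misses T2 and answers T3. About half of that parent's two-month service use is unobserved and has to be imputed, and any month-1 adverse event, serious or not, is never asked about. An event might still come to light if the parent volunteers it, but the plan does not ask. The half follows from the schedule and the stated recall, with T3 assumed on time.

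How many parents are involved is unknown, and so is the size of any gap or overlap from late answers, which also rests on the unstated assumption that the month is counted back from the day of answering. The primary outcome, its analysis and the sample size are not touched. This is an inexpensive improvement to data collection, worth making for the harms data above all.

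**What to change.** Change the recall for the CA-SUS and the adverse-event questions in both the resource-use item and the Harms section:

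- at T2: *since you joined SPARKLE*;
- at T3: *since your last completed SPARKLE survey*, or *since you joined SPARKLE* if T2 was not completed.

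Qualtrics should insert the actual date, so that parents need not work it out. The same wording closes gaps and removes overlaps when a survey is answered late.

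The cost is one piped date and one branch in an online survey. The downside is a two-month recall for parents who missed T2, and a reported interval that varies with the day of answering; how the economic analysis treats that variation can be left to the analysis plan. The change does nothing for a parent who misses T3, whose month 2 remains ordinary missing data.
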